#### Follow up FGDs and IDI.

We will **conduct a follow-up qualitative study** (FGDs and IDIs) post-intervention among implementers and participants to evaluate their intervention experiences and seek a more profound understanding or explanation for some of the survey findings. We will seek to know YGBMSM’s experiences with participating in the intervention, HPART experiences, and factors that remain a barrier to HPART despite enrolling in the study. We will seek to understand HCW experiences with delivering or taking part in the intervention and how that has translated to improved service delivery or otherwise in the HCF. CSO providers will also explain their experiences and recommendations for improving the intervention for a scale-up.

#### Data analysis.

We will use the intent-to-treat (ITT) technique to analyze data. We considered other methods (e.g., per protocol approach), but ITT is less biased since all participants are assessed whether they received the intervention or not. Data collected will be exported to Stata for cleaning and further analysis. Using the Monte Carlo Markov Chain approach based on a multivariate normal distribution of items, we will assess missing patterns in the instrument and impute missing responses with at least 70% of responses. Instruments scores will be calculated with observed and imputed responses. We will summarize the characteristics of participants and calculate Cronbach’s alpha to check internal reliability within scales. We will calculate a mean with a confidence interval for the variables and proportions of responses to the primary and secondary outcome variables. Variables with skewed distribution will be considered for being log-transformed or categorized in ordinal form. We will run inferential statistics such as paired t-test to compare pre-and post-means, McNamara’s test to compare pre-and post-proportions, and correlation analysis to examine the relationship between variables. We will also develop longitudinal models of the outcomes repeatedly measured at baseline, 3, 6, and 9 months post-intervention using a generalized linear mixed effect model (GLMM) with random intercept and peer group, which incorporate ICCs. The GLMM will include time-group interaction to estimate the intervention effect and pre-post changes. The GLMM will consist of all completed observations and drop-outs observed at least once post-intervention. Thus, we will not miss any individuals unless they are entirely missing at all post-intervention periods. Residuals will be assessed for normality assumption and influential outliers diagnosed with leverage, Cook’s distance, and DFFIT. The GLMM will be replaced with logistic and Poisson regressions with random effects when an outcome is binary and count data. We will repeat the same models separately for each site and compare the effect sizes between the sites. When we find any demographics, which are not equivalent between the two interventions, they will be included in the model as covariates. Acceptability, feasibility, and appropriateness will be evaluated with descriptive statistics of the implementation outcomes. **The process defined in AIM**1 will be used to analyze the follow-up qualitative data.

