#### Criteria:

The person must be between 18 to 25 years old, currently identifies as a cis-gender man, have had sex with another man within 8 months before engaging with the recruitment team, and must reside within a slum in the Accra metropolitan area. **Randomization**. When we complete the recruitment and baseline survey, we will stratify peer groups by the number of peer members and give a group ID to each peer group. Within each stratum with an equal number of peers, we will randomly select groups for intervention using simple random sampling. Thus, we will keep equal samples and peer groups between the two study arms.

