#### Potential challenges and solutions.

**Retention of participants.** Since we will be working with young adults and socially vulnerable persons, there is a high possibility that some of them will be mobile. As such, we will ensure we invite participants who are sure of their availability during the study period. We will also follow up periodically to check on their plans, and device means to ensure continuity. **Safety and security.** Although safety issues can affect retention, we have successfully established structures for all components of our studies that have provided participant security for over a decade^34,73,74,81,98^. Our partner organizations have activist and legal connections in place for externalities. We also get support from Ghana’s health and security services in case of external threats (we did not have to activate these security and legal structures as we have not encountered external threats in the previous works.

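### The mixed model leaves out randomised YGBMSM who have only a baseline survey, although the plan declares intent-to-treat and models baseline as an outcome time

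*Protocol article*

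**What the plan says.** All references are to the protocol article.

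- **Principle.** The Data analysis section under Appraisal of intervention opens with "We will use the intent-to-treat (ITT) technique to analyze data". It prefers this to a per-protocol approach because "ITT is less biased since all participants are assessed whether they received the intervention or not".
- **Who enters the model.** The same section then says: "The GLMM will consist of all completed observations and drop-outs observed at least once post-intervention". It adds: "Thus, we will not miss any individuals unless they are entirely missing at all post-intervention periods".
- **What is modelled.** It plans "longitudinal models of the outcomes repeatedly measured at baseline, 3, 6, and 9 months post-intervention", and "The GLMM will include time-group interaction to estimate the intervention effect and pre-post changes". Baseline is thus an outcome time in the model, not only a covariate.
- **When baseline is taken.** For YGBMSM, the Randomization text under Criteria begins: "When we complete the recruitment and baseline survey, we will stratify peer groups by the number of peer members". Group IDs and random selection follow.
- **Expected loss.** The Power section allows 10% attrition (240 to 216) and does not say when it occurs. Potential challenges and solutions says of these young men that "there is a high possibility that some of them will be mobile".
- **Imputation.** The only imputation described fills in missing responses within instruments that are at least 70% answered. It does not reach a person with no follow-up survey.

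**The concern.** The two sentences that define the model's membership exclude anyone with no survey at 3, 6 and 9 months. Whether a man is excluded is decided after randomisation, so the arms being compared are no longer the arms that were randomised. The set is a modified intent-to-treat set under the name of intent-to-treat.

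The exclusion is also unnecessary. The interaction is measured against each arm's baseline mean. If men with poor baseline scores leave early, the remaining men start from a better mean and regress towards the overall mean at follow-up. If this happens to a different extent in the two arms, the difference goes into the estimated effect. A likelihood model that keeps the baseline-only rows can correct for loss that depends on baseline. A model that deletes them cannot.

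Unequal loss is plausible but not established. The intervention arm is asked to attend a three-day weekend retreat, and the control arm waits nine months. The result is meant to inform a later full-efficacy trial, so a distorted estimate would carry forward.

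**Working it through.** **1. The plan's own figures.** Inputs from the Power section: ICC 0.04, 8 per friend group, 120 per arm, effect 0.50 SD, 5% significance (taken as two-sided).

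- Design effect = 1 + (8 − 1) × 0.04 = 1.28.
- Effective n per arm = 120 / 1.28 = 93.75. Power = Φ(0.50 / √(2/93.75) − 1.96) = 92.8%, against 92.7% stated.
- After 10% attrition: 108 / 1.28 = 84.4 per arm, power 90.1%, against 90% stated.

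The sample size is not at issue. If all the attrition were early, 240 − 216 = 24 men would leave the model.

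**2. Formula for the bias.** Let the baseline score be Y0 ~ N(0, 1) in both arms, with higher scores better. Let the follow-up score be ρY0 + error + 0.50 × arm. Early loss depends only on Y0 (missing at random). Let mI and mC be the mean baseline of the men who stay in each arm.

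- *Baseline-only men dropped:* mean change among stayers is 0.50 × arm − (1 − ρ)m, so the estimated effect is 0.50 − (1 − ρ)(mI − mC).
- *Baseline-only men kept:* the baseline mean is estimated from everyone (0). The likelihood adjusts the follow-up mean by ρ times the stayers' baseline excess, so the estimated effect is 0.50.

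**3. Results.** Assumed: ρ from 0.4 to 0.6, and loss weighted to low baseline with a log-odds slope of 1.2 per SD. The table shows the estimated effect when baseline-only men are dropped.

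| Early loss, intervention v control | Loss related to baseline in | mI | mC | ρ = 0.4 | ρ = 0.5 | ρ = 0.6 |
|---|---|---|---|---|---|---|
| 10% v 10% | both arms | 0.105 | 0.105 | 0.50 | 0.50 | 0.50 |
| 6% v 4% | both arms | 0.065 | 0.044 | 0.49 | 0.49 | 0.49 |
| 7.5% v 2.5% | both arms | 0.080 | 0.028 | 0.47 | 0.47 | 0.48 |
| 15% v 5% | both arms | 0.152 | 0.055 | 0.44 | 0.45 | 0.46 |
| 15% v 5% | intervention only | 0.152 | 0 | 0.41 | 0.42 | 0.44 |
| 20% v 5% | intervention only | 0.197 | 0 | 0.38 | 0.40 | 0.42 |

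Example, fourth row at ρ = 0.5: 0.50 − 0.5 × (0.152 − 0.055) = 0.45.

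If the men who leave the intervention arm are instead those with good scores (slope −1.2, 15% v 5%, intervention only), the sign reverses: 0.59, 0.58 and 0.56. An outlying case, equal 10% loss with slopes of 1 in opposite directions in the two arms, gives 0.41 at ρ = 0.5 and 0.37 at ρ = 0.3. Nothing in the protocol points to that pattern.

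**4. Check by simulation.** Generalised least squares with 200,000 per arm, ρ = 0.5 and slope 1, in four scenarios: with baseline-only men kept, 0.501 to 0.505; with them dropped, 0.459, 0.410, 0.417 and 0.504, against closed-form values of 0.457, 0.409, 0.413 and 0.500. The friend-group effect was left out of both calculations.

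**5. Scale.** At ρ = 0.5 with 108 per arm, the standard error of the change contrast is √(2 × 2(1 − 0.5)/108) = 0.14 SD before the design effect.

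**The case against.** **The intent-to-treat sentence is about receipt of treatment, not missing data.** It contrasts with per-protocol, and the next rule openly states who is left out. This is fair in part. Men who skip the retreat but answer any follow-up survey are analysed as randomised, as is a man who misses month 3 and returns later. Nothing is concealed. But the rule still excludes randomised men for whom the model has an outcome value, and at the least the set is misnamed.

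**The larger biases need stacked assumptions.** This stands. The protocol gives 10% attrition in total, with no timing and no split by arm. The 15% v 5% rows make all of it early and three times as common in one arm. The 20% v 5% row averages 12.5% and so exceeds the plan. The protocol also describes mitigation: it will invite men who are sure of their availability and will check on their plans periodically. A reader might infer that the effect will be materially understated. The documents do not support this: neither the size nor the direction can be known from them, and zero is a possible value.

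**Recovery of 0.50 follows from the set-up.** Also true. Loss was made to depend on observed baseline only. If loss depends on unobserved follow-up outcomes, keeping the baseline rows does not remove the bias.

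**Some primary outcomes gain nothing.** PrEP and ART biomarkers come from routine facility visits, and a man on neither drug at baseline has no baseline adherence value. The calculation also covers a continuous score only, whereas binary and count outcomes get logistic or Poisson models.

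**Healthcare workers.** A reader might extend the full argument to them. The protocol plans a baseline survey for them but does not place it before facility randomisation, so the argument is firm for YGBMSM only.

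**Conclusion.** The point holds for YGBMSM and for outcomes with a baseline value. The plan states a rule that discards usable rows because of a post-randomisation event, while claiming intent-to-treat. This is explicit text, not a detail left to a later analysis plan.

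The consequence is conditional. On a true effect of 0.50 SD:

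- no bias if early loss and its dependence on baseline are the same in both arms;
- about 0.01 to 0.06 SD for moderate differences between arms;
- about 0.06 to 0.12 SD for 15-20% v 5% early loss that is baseline-related in the intervention arm only.

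At ρ = 0.5 the moderate cases amount to less than half of one standard error, and the one-arm cases to roughly half to three quarters of one. These sizes rest on assumed loss patterns, slopes and correlations, and on missing at random. The change is worth making because it costs almost nothing, not because a serious distortion has been shown.

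**What to change.** In the Data analysis section under Appraisal of intervention, replace the sentence that defines the model's membership with:

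> The GLMM will include every randomised YGBMSM with any outcome observation, including baseline only, analysed in the arm assigned.

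Delete the sentence that follows it. Add that the number of men with baseline only will be reported by arm. State that including them protects under missing at random only, and adds nothing for outcomes without a baseline value.

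Apply the same membership rule to healthcare workers who have a baseline survey, without claiming that this survey precedes facility randomisation.

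The cost is a few lines of text. No extra participants or data are needed, and the same model accepts the baseline rows. The article says recruitment has not begun, so the change can be made prospectively.

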### Power.

#### YGBMSM:

We perform the power analysis to detect the difference in intervention outcomes using a sample measurement scale (HIV-ASES)^101^ between intervention and control (n=240, control arm=120, intervention arm = 120) by adjusting the Intraclass correlation coefficient (ICC) for the friend group. In a similar setting, a network membership explained 4.08% (i.e., ICC=0.04) of the total variance in outcomes^102^. The ICC of 0.04 and 8 individuals in a friend group will produce the design effect (DE) of 1.28. Approximately 15 peer groups will be randomly assigned to each study arm. A DE of 1.28 and a sample of 240 (120 per arm) will have 92.7% power to detect the medium effect size of 0.50 at a 5% significance level. The medium effect size of 0.50 implies a 5.6 point (SD=11.2) on the outcomes and 0.62 points (SD=1.23) based on standard deviations from HTAS. The sample size of 120 in the intervention group will have 99% and 82% powers to detect the medium and small effect sizes of 0.50 and 0.30, respectively, on the outcome changes within the group. With a 10% attrition rate, 216 participants will have 90% power to detect the medium effect size of 0.50, and 108 participants receiving the intervention will still have 99% for the medium effect size after adjusting for ICC of 0.04.

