### Measures.

#### Demography, HIV testing, and ISD descriptive variables.

We will assess important baseline characteristics for describing the sample, including age, income, gender, education, ethnicity, relationship status, religion, sexual orientation, sexual behavior, HIV knowledge, HIV testing, PrEP and ART readiness, and history. Experiences of ISDs, access, and utilization of health and social services, civic engagement, and neighborhood. **Primary outcomes:** At baseline, 3, 6, and 9 months, we will measure the preliminary efficacy of LAFIYA. We will measure knowledge of HIV and HPART; and willingness to adhere to HPART pre and post-intervention. HPART adherence characteristics (rates, time, mode, location) and biomarkers (Table 2). **Secondary outcomes:** For ISD reduction, we will measure internalized and interpersonal level ISD at baseline and post-intervention surveys among YGBMSM. We will measure HCF-level ISD to understand participant experiences at baseline and changes in HCW stigmatizing beliefs and practices (Table 2). **Implementation outcomes:** We will measure acceptability, appropriateness, and feasibility using expanded Proctors validated measures at pre-immediate and post-intervention surveys at all levels (Table 2)^103^.

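### The Poisson rule for count outcomes makes no allowance for visit-to-visit over-dispersion, so the time-by-group test would reject too often for any outcome that proves to be an over-dispersed count

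*Protocol article*

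**What the plan says.** The Data analysis section under Appraisal of intervention proposes longitudinal models for "outcomes repeatedly measured at baseline, 3, 6, and 9 months post-intervention", fitted "using a generalized linear mixed effect model (GLMM) with random intercept and peer group, which incorporate ICCs". It identifies the treatment effect as follows: "The GLMM will include time-group interaction to estimate the intervention effect and pre-post changes". For other outcome types it adds: "The GLMM will be replaced with logistic and Poisson regressions with random effects when an outcome is binary and count data".

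The section names no negative binomial alternative, dispersion parameter, visit-level random effect, robust variance or dispersion check. Its diagnostics are residual normality and influence measures. It says that skewed variables will be considered for log-transformation or ordinal grouping.

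The Measures section lists among the primary outcomes "HPART adherence characteristics (rates, time, mode, location) and biomarkers", with the detail in Table 2, which is not in the text at hand.

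**The concern.** The time-by-group interaction compares changes within the same men. A person intercept and a peer-group intercept cancel from that comparison, so its model-based standard error rests on the Poisson assumption that variance equals mean at each visit, given the intercepts. If a man's count moves between visits by more than that, the standard error is too small and the test rejects too many null trials. This is separate from friend-group clustering and would arise with an ICC of zero.

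The article says that the results will feed a later full-efficacy trial. A false signal on a count outcome, such as tests taken or doses missed, could therefore shape that trial. Those two examples are assumptions, since no count is named.

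**Working it through.** **Inputs from the article.** Power section, YGBMSM: "n=240, control arm=120, intervention arm = 120"; "Approximately 15 peer groups will be randomly assigned to each study arm"; "The ICC of 0.04 and 8 individuals in a friend group will produce the design effect (DE) of 1.28". Data analysis section: four visits, a random intercept and peer group, and the time-by-group interaction as the treatment effect.

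**The plan's own figure.** Design effect = 1 + (8 − 1) × 0.04 = 1.28. Effective number per arm = 120/1.28 = 93.75. Power for 0.50 SD, two-sided 5%: Φ(0.5 × √(93.75/2) − 1.96) = Φ(1.463) = 92.8%, against 92.7% stated. With 108 per arm it is 90.1%, against 90%. Both reproduce. They concern a continuous scale, so this point leaves them untouched; the article gives no power or error rate for a count.

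**Assumed inputs.** Mean count per wave μ, and visit-level (gamma) variance v. The variance/mean ratio within man and visit is then φ = 1 + μv.

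**Analytic size.** The single-contrast test has true size 2 × (1 − Φ(1.96/√φ)):

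| μ | v = 0.25 | v = 0.5 | v = 1 |
|---|---|---|---|
| 0.3 | 5.9% | 6.8% | 8.6% |
| 1 | 8.0% | 11.0% | 16.6% |
| 2 | 11.0% | 16.6% | 25.8% |

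For example, μ = 2 and v = 0.5 give φ = 2, 1.96/√2 = 1.386, and size 16.6%. For the joint test of all three follow-up interactions, the size is P(χ²₃ > 7.815/φ): 15.7% at φ = 1.5 and 27.2% at φ = 2.

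These figures are somewhat low, because men with high stable rates weigh more and have larger φ. With φ set to 1.5 at a mean of 2, and person and group log-SDs of 0.6 and 0.15, the average ratio in the simulated data was 1.89. The formula then gives 15.4%, close to the simulated 14-15%.

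**Simulated null trials, 30 groups of 8, model-based standard errors.**

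- *Two waves, person-conditional Poisson test, 1,500 trials per setting, v = 0, 0.25, 0.5, 1.* Mean 1: 5.6%, 9.1%, 12.7%, 22.9%. Mean 2: 5.0%, 14.3%, 20.5%, 32.8%.
- *Four visits, random-intercept Poisson fitted by quadrature, mean 2, 500-600 trials per setting.* With no over-dispersion: 5.5% for the 9-month interaction and 4.7% for the joint test. At v = 0.25: 14-15% and 23-24%. At v = 0.5: 23-24% and 41-44%. At v = 1: 34% and 62%.
- *A further simulation of single-contrast size over several means.* About 5% with no over-dispersion, 7-10% at mean 0.3, 11-20% at mean 1 and 14-35% at mean 2.

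**Remedies, checked on simulated data.**

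- *Random-intercept negative binomial, mean 2, 300 trials per setting, v = 0, 0.25, 0.5.* Single contrast: 6%, 6%, 5%. Joint test: 6%, 4%, 5%. Poisson on the same data gave 6%, 16%, 22% and 7%, 25%, 45%. With 300 trials, the Monte Carlo standard error at 5% is √(0.05 × 0.95/300) = 1.3 percentage points.
- *Poisson with robust errors clustered by peer group, four visits.* Single contrast: 5-8%. Joint test: 9-13%; an excess remains with 30 clusters and a chi-square reference.

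**The case against.** The strongest reply is that the article establishes none of the three conditions the fault needs.

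- **A count outcome.** None is visible. An adherence rate may well be a proportion, which would go to the logistic model. A reader might infer that the primary HPART rates themselves have standard errors that are too small. The documents do not support that, because the outcome definitions sit in a table that is not shown. This part of the objection stands.
- **Over-dispersion.** No mean or dispersion is given. Rare events inflate the error little, and bounded counts can be under-dispersed: a variance/mean ratio of 0.8 gives 2.8%, which is conservative. A blanket claim of gross inflation is therefore unsupported. This also stands.
- **Model-based errors and intercepts alone.** The text does not say that the random effects are intercepts only, and it names no variance estimator. A visit-level effect or robust errors would be compatible with the sentence. The narrower structure is the natural reading of the GLMM sentence, but it is an inference.

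The reply also notes that skewed counts might be log-transformed or grouped. That option is discretionary and leaves the Poisson rule in place for whatever remains a count.

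Finally, a condensed article may leave detail to a fuller document. Here, however, the article does not stay silent: it chooses a distribution. A nearly free alternative that contains Poisson as a special case held its level in the simulations, with and without over-dispersion. So the point survives as a conditional one.

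**Conclusion.** The point holds in conditional form. Where an outcome proves to be a count that varies between visits beyond Poisson, and model-based standard errors are used, the time-by-group test as written is anti-conservative.

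All magnitudes depend on assumed means and dispersions. The single-contrast error rate is about 5% with no visit-level over-dispersion and about 7-10% at 0.3 events per wave. It is roughly 10-35% at 1-2 events per wave with visit-level variance 0.25-1. A joint test over the three follow-ups does worse.

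Severity is minor to moderate. The fault is confined to outcomes that prove to be over-dispersed counts, the trial tests preliminary efficacy, and the rule can be changed before analysis. Continuous and binary outcomes and the published power figures are not affected.

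**What to change.** In the Data analysis section, for count outcomes, replace Poisson by a negative binomial mixed model with the same fixed effects (including the time-by-group interaction) and the same person and peer-group random effects. Poisson is its special case of no over-dispersion, so little is lost if the counts are well behaved.

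Alternatively, keep Poisson and state that variances will be robust to over-dispersion and clustered by peer group. Add a small-sample correction, because about 30 groups left 9-13% on the joint test without one.

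The cost is a sentence in the plan, a different Stata command, and somewhat wider intervals where counts are over-dispersed. No further data or participants are needed.
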